#### ***Artificial Intelligence Analysis***

Please see separate attachment detailing artificial intelligence methods.

#### ***Continuous Glucose Monitoring Analysis***

Concurrent glucose meter and sensor BG values will be compared by calculating both the mean difference (meter blood glucose minus sensor blood glucose) and mean absolute difference (absolute difference of the mean difference) between BG values, expressed both in mg/dL and as a percentage. A

Pearson correlation coefficient ( $r$ ) will be calculated for the entire set of meter–sensor pairs. Finally, paired M-S values will be plotted on a Clarke Error Grid.

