### Devices to be used

- Home hospital employs standard devices during the usual care of hospitalized patients. For example, a nebulizer machine.
- Home hospital additionally employs
  - Vital signs monitoring patch: Vital Connect VitalPatch (FDA cleared application/use, but new hardware and software updates are pending clearance)
    - As we have done in the past under IRB approval, we will use new Vital Connect VitalPatch hardware and VistaCenter software as they become available. The newest hardware, the VitalPatch 2.0, and newest software, VistaCenter 2.0 add core temperature, longer battery life, and connectivity for a blood pressure cuff and pulse oximeter. Importantly, these only represent new functionality, but

these versions are not FDA approved. There will be no decrement in our ability to monitor patients.

- Ambulatory infusion pump: Smiths Medical CADD Solis VIP (FDA cleared application/use)
- Point of care diagnostic meter: Abbott iSTAT (FDA cleared application/use) or Siemens Epoc (FDA cleared application/use)
- Ambulatory ECG: General Electric ECG (FDA cleared application/use)
- Massimo Rad-7 Rainbow Acoustic respiratory monitor (FDA cleared application/use)
- Digital stethoscope: Eko (FDA cleared application/use)
  - Our home hospital team plans to use this FDA cleared digital stethoscope to transmit near-real-time heart, lung, and abdominal sounds to a remote physician.
- Point of care ultrasound (POCUS)
  - Our home hospital team wants to improve the timeliness and efficiency of our radiology studies. The best way to do this is to add POCUS capabilities for our clinicians.
  - We will train our clinicians per standard Brigham protocols for POCUS, as approved by [name]. They will have standard oversight and overreading.
  - Point of care ultrasound device
    - Phillips Lumify Ultrasound (FDA cleared application/use)
      - We may use this device to assist clinicians with diagnosis and treatment. Examples include
        - insertion of a peripheral intravenous catheter;
        - assessment of heart and lung function; and
        - assessment of post-void residual
      - This system is already in use at Brigham.
- Continuous glucose monitor: Dexcom G6 (FDA cleared application/use at home, not in the acute setting with off-label cleaning procedure)
  - Continuous glucose monitoring in the acute setting has been shown to be safe and accurate, although further testing is ongoing.

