| Any glucose >300mg/dL, y/n                                                       | Dexcom device and EHR                                                       | Daily          |
| Any glucose <70mg/dL, y/n                                                        | Dexcom device and EHR                                                       | Daily          |
| Any glucose <40mg/dL, y/n                                                        | Dexcom device and EHR                                                       | Daily          |
| Capillary versus continuous glucose (see statistical methods)                    | Dexcom device and EHR                                                       | Daily          |

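### The protocol's gloss on the CGM mean absolute difference conflicts with its name: read literally it is the mean difference without its sign, so opposite sensor errors cancel

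*Protocol*

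**What the plan says.** The Continuous Glucose Monitoring Analysis, under Statistical methods in the Protocol, compares paired meter and sensor glucose values in four ways:

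- a mean difference, taken as meter minus sensor;
- a "mean absolute difference (absolute difference of the mean difference) between BG values", which like the first is to be "expressed both in mg/dL and as a percentage";
- a Pearson correlation that "will be calculated for the entire set of meter–sensor pairs";
- a plot: "paired M-S values will be plotted on a Clarke Error Grid".

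The parenthesis in the second item is the only definition of that statistic in the protocol. The glucose rows of the Quality: High-Value Care table list the capillary-versus-continuous comparison but only refer back to the statistical methods.

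As context, Devices to be used describes the sensor as "FDA cleared application/use at home, not in the acute setting with off-label cleaning procedure".

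**The concern.** The name mean absolute difference ordinarily denotes the average size of the paired errors: take the absolute value of each difference, then average. The parenthesis reverses the order: average first, then drop the sign. A sensor that reads high as often as it reads low would then score near zero however large its individual errors are.

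At stake is how the reported number is read. A reader who sees a mean absolute difference of a few mg/dL will take it as the typical error of a single reading. Under the literal definition it is only the size of the average bias, which the signed mean difference already gives.

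**Working it through.** The protocol states no sample size, error SD, bias or target for this analysis, so it has no figure to reproduce. The check compares the two definitions.

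**Notation.** For pair i, d_i = meter_i - sensor_i (the protocol's sign convention).

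- Mean difference: mean(d).
- As the parenthesis reads: A = |mean(d)|.
- As the name reads: B = mean(|d|).

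**Direction.** By the triangle inequality A ≤ B, with equality only when no two differences have opposite signs. The literal version can therefore understate the average error but never overstate it. A is also fully determined by mean(d), so it carries no new information.

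**Worked example (invented values).** Meter 100, 100, 200, 200; sensor 140, 60, 240, 160 mg/dL. The differences are -40, +40, -40, +40.

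- A = |0/4| = 0 mg/dL.
- B = (40 + 40 + 40 + 40)/4 = 40 mg/dL.
- In percent of the meter value, the signed mean is (-40 + 40 - 20 + 20)/4 = 0%, and the mean of absolute values is (40 + 40 + 20 + 20)/4 = 30%.
- Pearson r is 0.78, although every reading is wrong by 40 mg/dL.

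**Range under assumed normal errors.** Let the errors have bias b and standard deviation s. Then A tends to |b|, and

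B = s·√(2/π)·exp(-b²/(2s²)) + b·[1 - 2Φ(-b/s)].

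With b = 0 this reduces to B = 0.798·s. All values of b and s below are assumptions, in mg/dL.

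| Bias b | SD s | A, as written | B, mean of absolute differences |
|---|---|---|---|
| 0 | 10 | 0 | 8.0 |
| 0 | 15 | 0 | 12.0 |
| 0 | 25 | 0 | 19.9 |
| 0 | 30 | 0 | 23.9 |
| 0 | 40 | 0 | 31.9 |
| 5 | 25 | 5.0 | 20.3 |
| 10 | 10 | 10.0 | 11.7 |
| 20 | 40 | 20.0 | 35.8 |
| 20 | 10 | 20.0 | 20.2 |

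For the last row: 10 × 0.798 × exp(-2) + 20 × (1 - 2 × 0.02275) = 1.08 + 19.09 = 20.2.

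Simulation with 200,000 pairs per scenario agrees with the formula. At zero bias and SD 10, 20 and 40, A was 0.03, 0.04 and 0.15 and B was 8.0, 16.0 and 32.0. With meter values assumed to be about 170 (SD 50) mg/dL, B in percent form was 5.2%, 10.4% and 20.8%, while the literal version was at most 0.12%.

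The gap is therefore widest when scatter dominates and all but disappears when bias is large relative to scatter.

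**The case against.** **It is probably a slip.** The name already denotes the right statistic, the parenthesis is awkward (one does not take an absolute difference of a single mean), and the authors list it as a second quantity beside the mean difference, which suggests they did not mean an unsigned copy of the first. This is plausible. But the text then contradicts itself: an analyst who follows the parenthesis computes the wrong quantity, and one who follows the name departs from the stated definition. Nothing else in the protocol settles it. A statistical analysis plan, which was not available here, might, but the protocol sentence would still need correcting.

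**Individual errors are not hidden.** A reader might infer that an inaccurate sensor could pass unnoticed. The protocol does not support that. The Clarke Error Grid plots every pair and nothing cancels on it, and Pearson r also falls as scatter grows (0.98, 0.93 and 0.78 at SD 10, 20 and 40 in the simulation). It is true that the protocol promises only a plot, with no zone percentages, and that r measures association rather than agreement. That leaves the mislabelled number uncorrected, but it does not make the analysis blind.

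**Nothing stated depends on the figure.** A reader might also infer that a flattering number would justify using the sensor or reducing finger-stick checks. Devices to be used describes both without making either conditional on this analysis. The comparison is absent from the Study endpoints table and has no hypothesis, threshold or decision rule. This objection stands in full.

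**The percentage form is not spelled out.** The protocol does not say how the percentage is calculated. That it shares the problem follows only if the same parenthesis is applied to it, which is the natural reading but still a reading.

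**Conclusion.** The point holds as a definition error in one statistic. Read literally, the parenthesis gives |mean(meter - sensor)|, which contradicts the name, repeats the bias without its sign, and can only equal or understate the average paired error. Under assumed normal errors with no bias and SD 15 to 30 mg/dL, the reported value would be about 0 in place of 12 to 24 mg/dL. With bias 20 and SD 10 the two definitions are practically the same. The protocol supplies neither bias nor SD, so where the real data will fall in that range is unknown.

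The consequence is a mislabelled device-accuracy figure that is too favourable. The randomized remote-versus-in-person comparison and the listed study endpoints are not affected.

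**What to change.** Replace the parenthesis so that the mean absolute difference is the average over all meter-sensor pairs of |meter - sensor| in mg/dL, and state its percentage form as the average over pairs of |meter - sensor| / meter × 100. Keep the signed mean difference, labelled as the measure of bias. The Pearson correlation and the Clarke Error Grid can stay as planned; adding limits of agreement would be a separate preference and is not needed to correct this.

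The cost is one sentence of protocol wording. The same paired data are used and no clinical procedure changes. The reported figure will be the same or larger, never smaller.

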## Power analysis

### *Standard Home Hospitalization*

Our recent RCT data suggest that at 90% power, we will require 38 patients in each arm. However, we also have prespecified a smallest important difference of \$1000, for which we will need 144 patients in each arm at 90% power.

For 30-day readmission, we will require 110 patients in each arm at 90% power (23% vs 7%). If the effect size is indeed smaller, for example 23% vs 15%, we will need 528 patients in each arm. However, we will not be able to power around a smallest important difference of 3%, for which we would need 4006 patients in each arm.

For percentage with a safety event, we will require 641 patients in each arm at 90% power and 493 patients in each arm at 80% power (15% vs 9%).

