## Statistical methods

### *Home hospital vs traditional hospital*

#### *Quantitative*

We plan to form 3 different control groups (with groups listed in order of preference):

1. Patients who were deemed eligible for home hospital, but the service was full (and they were not enrolled subsequently if the service was no longer full);
2. Patients who were deemed eligible for home hospital, but lived outside of the 7.5-mile catchment area; and
3. Patients who were admitted to the hospital.

For each control group, we will use propensity score weighting, adjusting for covariates of interest (see table above), baseline functional status, and DRG. We will be cognizant of over-adjustment depending on our final sample size for each group above. If possible, we will use only group 1 above, as it is the strongest. If we have insufficient control group sample size, we may choose to combine groups 1 and 2 above.

The primary outcome (hospitalization cost) will be assessed using a generalized linear model assuming a gamma distribution with a log link. We will use a multivariable regression approach for secondary

outcomes, using logistic regression for binary outcomes and non-transformed linear regression for normally distributed continuous outcomes as appropriate.

We *a priori* plan to perform a subgroup analysis that does not involve any outlier participants, should this occur. We also *a priori* plan subgroup analyses by diagnosis, by age group, by disposition, by location of admission (e.g., ED, floor, clinic, and home), and by daily activity level. We also *a priori* plan to analyze our outcomes with means, but also with median and interquartile ranges, which are less subject to outlier effects. We may choose to employ non-parametric tests of significance should our data be nonparametric.

We *a priori* plan to adjust our secondary analyses using the Benjamini-Hochberg method. We *a priori* choose a false-discovery rate of 0.20.

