#### ***Early transfer to home hospital vs traditional hospital***

We plan to use the same statistical analysis as in the Standard Home Hospitalization methods noted above. However, we do anticipate requiring an additional variable that notes whether a patient was initially considered for home hospital care and was not eligible due to a full census, and then was later taken home when the home hospital service census allowed.

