### *Remote vs In-Person Care Analysis*

During our prior RCT of home hospital, patients experienced a mean of 0.09 (SD 0.29) adverse events during their home hospital admission. We believe the smallest clinically meaningful treatment difference would be 0.1 adverse events (i.e., from 0.09 to 0.19 adverse events per patient). In this non-inferiority trial ( $\alpha=0.025$ , power 80%, non-inferiority limit 0.1 events), we would require 210 patients (105 in each arm). Because of clustering, the actual required sample size will be larger. With 5 home hospital physicians ( $\rho$  0.01), we require 260 patients (130 in each arm). We consistently enroll 25 patients monthly, leaving us with sufficient power after about 11 months.

We plan an interim futility analysis. After 130 patients have completed the remote vs in-person care study, we will calculate the difference in adverse event rates between the two arms. If the difference is 0.10 or higher (with the higher rate in the intervention arm), then we will stop the trial for futility. This rule will reduce the power about 2%.

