### *Early Transfer*

To calculate sample size, we used simulation in the PASS program (NCSS LLC, Kaysville, UT) comparing gamma distributed costs, with baseline data based on the home hospital RCT. With 324 patients in each arm of the study, even accounting for intraclass correlation by Home Hospital physician (intraclass correlation coefficient 0.01, cluster size 65), we will have 82% power to detect a relative decrease of 21% in total costs of care, smaller than the 27% decrease seen in this outcome in the Home Hospital RCT and close to the smallest reduction that would be considered clinically important. This sample size will also provide 80% power to detect a 43% reduction in readmission (again smaller than that seen in the Home Hospital RCT), and 81% power to detect non-inferiority for adverse events (assuming a baseline of 0.15 events per patient).

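### The binary-outcome sample sizes for home versus traditional hospital allow nothing for shared home hospital physicians, although the parallel early-transfer calculation does and the analysis both comparisons share names no physician term

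*Protocol*

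**What the plan says.** All references are to the protocol.

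- **Power analysis, Standard Home Hospitalization.** For cost, 38 per arm is given from earlier trial data; for a smallest important difference of $1000, "we will need 144 patients in each arm at 90% power". For 30-day readmission: 110 per arm (23% vs 7%), 528 (23% vs 15%) and 4006 (a 3-point difference). For the percentage with a safety event (15% vs 9%), "we will require 641 patients in each arm at 90% power and 493 patients in each arm at 80% power". Neither clustering nor weighting is mentioned.
- **Power analysis, Remote vs In-Person Care.** "Because of clustering, the actual required sample size will be larger". With five physicians and a correlation of 0.01, the total rises from 210 to 260.
- **Power analysis, Early Transfer.** With 324 per arm, power is given "even accounting for intraclass correlation by Home Hospital physician (intraclass correlation coefficient 0.01, cluster size 65").
- **Statistical methods, Home hospital vs traditional hospital.** Propensity score weighting is specified, and "The primary outcome (hospitalization cost) will be assessed using a generalized linear model assuming a gamma distribution with a log link"; secondary outcomes use logistic or linear regression. No physician term is named.
- **Statistical methods, Early transfer.** "We plan to use the same statistical analysis as in the Standard Home Hospitalization methods noted above", with one extra variable for patients first turned away because the census was full.
- **Statistical methods, Remote vs In-Person.** Because a home hospital team is shared among patients, the analysis clusters by home hospital physician with estimating equations.
- **Study endpoints table.** Standard home hospitalization and early transfer have the same design type: a prospective intervention group with a retrospective propensity-weighted evaluation.

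**The concern.** Two comparisons of home with traditional hospital share a design type and a declared analysis but are powered on different bases. One allows for physician clustering; the other does not, and no reason is given. The reason offered for clustering in the randomised comparison, that one team treats many patients, applies equally to the home arm of the standard comparison.

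There is a second mismatch within early transfer: its sample size assumes clustering, while its analysis is copied from a section that has no place for it.

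At stake are the powers quoted for readmission and safety, possibly the power for the primary cost outcome, and the width of the intervals if the models are fitted as though patients were independent.

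**Working it through.** **Inputs.** Rates, sizes and stated powers are from Power analysis, Standard Home Hospitalization. ICC 0.01 and cluster size 65 are from Early Transfer. Five physicians is from Remote vs In-Person Care, and 324/5 = 64.8 shows that Early Transfer uses the same number. Two-sided 0.05 and 1:1 allocation are assumptions, since the section states neither. The 3-point difference is read as 23% vs 20%.

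**Step 1: reproduce the stated sizes.** With d = p1 − p2 and p̄ the mean rate,

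n = [1.96·√(2p̄(1−p̄)) + z·√(p1(1−p1) + p2(1−p2))]² / d², then with continuity correction n_c = (n/4)·[1 + √(1 + 4/(n·d))]².

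| Comparison | Power | Uncorrected | Corrected | Stated |
|---|---|---|---|---|
| 23% vs 15% | 90% | 504 | 528 | 528 |
| 23% vs 20% | 90% | 3939 | 4006 | 4006 |
| 15% vs 9% | 80% | 460 | 493 | 493 |
| 15% vs 9% | 90% | 615 | 648 | 641 |
| 23% vs 7% | 90% | 103 | 115 | 110 |

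Three match exactly and 641 is within about 1%. The 110 lies between the two versions; rounded rates may explain it. There is no room in these figures for a design effect.

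**Step 2: put the protocol's ICC in the home arm only.** Traditional-hospital controls have no home hospital physician, so only the home arm is inflated. With DE = 1 + (m − 1)·0.01,

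SE² = [p1(1−p1) + DE·p2(1−p2)] / n (p2 = home arm), and power = Φ(d/SE − 1.96); with continuity correction, d is reduced by 1/n.

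Example, 641 per arm and m = 65: DE = 1.64; SE² = (0.1275 + 1.64 × 0.0819)/641 = 0.000408; SE = 0.0202. Power = Φ(0.06/0.0202 − 1.96) = 84%, or 82% with correction.

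Example, 641 per arm and five physicians: m = 641/5 = 128.2; DE = 2.27; SE = 0.0221; power 77%, or 75% with correction.

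| n per arm | Stated power | m = 65 | m = n/5 (DE) |
|---|---|---|---|
| 641 (15% vs 9%) | 90% | 82-84% | 75-77% (2.27) |
| 493 (15% vs 9%) | 80% | 71-74% | 67-70% (1.98) |
| 528 (23% vs 15%) | 90% | 82-84% | 77-79% (2.05) |

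Ranges are with and without continuity correction. With DE = 1 the same formula returns 90-91%, 80-83% and 90-91%, so the fall comes from the clustering. At 110 per arm (23% vs 7%), five physicians gives m = 22, DE = 1.21 and power of about 88-91%: little changed.

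**Step 3: cost, conditionally.** No SD is given, so 144 cannot be reproduced. If it too has no allowance, 90% power implies a non-centrality of 1.96 + 1.28 = 3.24. With equal variances, the average inflation is (1 + DE)/2.

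- m = 144/5 = 28.8: DE 1.28, average 1.14, power Φ(3.24/√1.14 − 1.96) = 86%.
- m = 65: DE 1.64, average 1.32, power 81%.

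**Step 4: early-transfer analysis.** At 324 per arm, m = 65, home arm only, the average inflation is 1.32. If the model were fitted with a variance that ignores clustering, the two-sided error would be 2·[1 − Φ(1.96/√1.32)] = 8.8% against 5%.

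**The case against.** Several stronger readings are tempting, and the protocol does not support them.

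- *The plan says outcomes in the standard comparison cluster by physician.* It does not. It says so for the randomised comparison and assumes it in the early-transfer power. The extension rests on the shared-team rationale, the common design type and the common analysis.
- *Both arms should be inflated.* That would take 641 per arm below 60% with five physicians. But controls have no home hospital physician, and no ICC for hospital clinicians is given.
- *The standard errors are too small.* A sample-size formula does not affect a standard error, and the methods section fixes no variance estimator. A statistical analysis plan that is not shown may set a clustered one. The 8.8% holds only under a naive variance.
- *The stated power will not be delivered.* The section lists required numbers under several scenarios and sets no enrolment target. The Rationale reports over 300 home patients already enrolled. If 300 per arm were analysed (control numbers are not stated), the Step 3 method gives about 98% for the $1000 difference.

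It is also fair that 641, 493 and 528 concern secondary outcomes, which are judged at a false-discovery rate of 0.20 and not at two-sided 0.05. Holding physicians at five is a further assumption, since the background says more staff can be hired; cluster size 65 is the milder case. The loss from weighting cannot be computed from the document.

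These points limit the size and wording of the concern. They do not explain why two parallel comparisons are powered differently, or why early transfer is powered with a term that its analysis lacks.

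**Conclusion.** The concern stands as an internal inconsistency with a moderate effect on stated power. On the protocol's own ICC, with home-arm clustering only, the 90% claims at 641 and 528 per arm become roughly 75-84%, and the 80% claim at 493 becomes roughly 67-74%. The figure at 110 per arm is little affected. For the primary cost outcome, about 81-86% instead of 90% at 144 per arm is conditional on that number containing no allowance, which cannot be verified.

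The results rest on two-sided 0.05, 1:1 allocation, ICC 0.01 carried over from early transfer, and a cluster size of either 65 or one fifth of the arm. The inflated error rate for early transfer is a conditional warning, not a demonstrated fault.

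**What to change.** - **Power analysis, Standard Home Hospitalization:** keep the sizes and restate the power at each, using ICC 0.01 in the home arm with the cluster size stated. Say whether the cost figures contain any allowance, and give the SD. Note that propensity weighting will lower the effective sample size by an amount not yet known. Enrolment stays as it is.
- **Statistical methods, Home hospital vs traditional hospital and Early transfer:** account for home hospital physician in the home arm of the weighted models, for example by a home-arm physician random effect or a cluster-robust variance with a small-sample correction, so that the analysis matches the basis of the early-transfer power.

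The cost is some wording and a modest model change, with no additional patients. Stated power becomes less favourable and intervals somewhat wider. With about five physicians, all in one arm, either cluster method has limited reliability, and the protocol should say so.
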